**Methods and analysis:**

This is a protocol for a prospective cross-sectional matched-subject observational study. We will include 20 adults undergoing unilateral primary TKA for painful advanced knee osteoarthritis, their contralateral pain-free knees as internal controls and 20 age and sex matched healthy controls without joint pain or functional limitation. All participants will undergo standardised clinical assessment and complete pain and psychological PROMs. In patients with TKA, venous blood will be collected pre-operatively. During TKA surgery, synovial fluid will be aspirated from the painful operated knee and the contralateral pain-free knee. Healthy controls will provide a single venous blood sample at a hospital visit. Peripheral blood mononuclear cells and synovial fluid mononuclear cells will be stimulated ex vivo with toll-like receptor 2 and 4 agonists to quantify IL-1β release. In parallel, hyperspectral imaging will characterise unstimulated immune cell phenotypes. Multivariable statistical and machine-learning approaches will relate biomarker profiles to pain and psychological PROMs.

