### Clinical assessment and questionnaires

The primary outcome included EC50 (concentration-response parameter: concentration which produces 50% of the maximal effect) for IL-1β release, to determine the responsiveness of PBMC and SFMC to LPS and PAM3 stimulation. Osteoarthritis severity of the painful knee will be graded by an orthopaedic surgeon based on Kellgren-Lawrence and self-assessed pain scores will be determined by the patient preoperatively for both knees using the NRS-pain scores. Additionally, preoperative mental state will be assessed by completing two Patient Reported Outcome Measures (PROM): the Hospital Anxiety and Depression Scale (HADS) questionnaire,^34^ and the Pain Catastrophizing Scale (PCS) questionnaire.^35 36^ The HADS consists of an anxiety (HADS-A) and a depression (HADS-D) subscale, each including seven items scoring 0–3, resulting in a total maximum score of 21 per subscale. Scores of 8–11 are considered borderline anxiety or depression, whereas scores>11 are considered presumable anxiety or depression.^37^ In this study, an HADS-A or HADS-D score ≥8 will be categorised as the presence of anxiety or depression, respectively.^34 38^ The PCS is a validated questionnaire consisting of 13 statements regarding feelings and thoughts during experiencing pain.^35 36^ Patients rate these statements on a 5-point Likert scale ranging from ‘not at all’ to ‘all the time’ with the total score ranging from 0 (no catastrophising) to 52 (severe catastrophising). A score of 30 or higher is considered clinically relevant catastrophising;^36 39^ as such, patients will be considered pain catastrophizing (PC) or non-PC patients.

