#### Primary outcome analysis: painCELL data

Concentration-response curves from the in vitro innate immune stimulated IL-1β release from PBMCs and SFMCs are calculated using GraphPad Prism version 8 (MathWorks; Natick, Massachusetts, USA). Differences between pain-free controls and painful symptomatic osteoarthritis patients (within the same patient for synovial fluid samples and a different patient for blood samples) will be assessed on EC_50_, Hillslope and ‘Top’ (or E_max_). The ‘Bottom’ value will be constrained to a constant of 0. An F-test in GraphPad Prism will be performed to determine if these values should be the same or different between the participant groups. The goodness of fit obtained from the TLR-2 stimulation is not sufficient to warrant presentation in the results, owing to lower-than-expected cytokine expression in the assays.

The painCELL assay cytokine data will be combined with osteoarthritis severity and NRS-pain reports, as well as other demographics (such as mental state) for each participant in a data file. Additional parameterisation of the data set will be performed to capture the delta change in cytokine release between low and high concentration innate immune challenges and between these delta values and the steepness of the concentration response.

First, a feature selection (dimensionality reduction) step will be performed to remove highly correlated variables, by examining the correlation matrix and applying the ‘Bivariate Correlations’ function to identify and exclude variables with Pearson Correlation coefficients greater than 0.8. For each specific hypothesis test, data subsets will be created using the ‘Select Cases’ function to exclude irrelevant subject data (eg, when testing the model for Healthy synovial sample Controls and the contralateral painful knee, Healthy blood sample Controls data will be excluded).

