For analysis, a randomised approach with at least a 20% holdout validation and test dataset will be employed. The dataset will be split to ensure that the test dataset is not included in the model training phase. For the categorical selection hypotheses, several classification techniques will be applied in parallel, expected to include: Linear Discriminant Analysis (LDA), Classification and Regression Trees, K-Nearest Neighbours, Support Vector Machine and Random Forest models. The best-performing model will be identified based on the highest accuracy and lowest error rate, for which a confusion matrix will then be created.

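### Accuracy is the only stated rule for choosing the painCELL classifier; if the dichotomised PROMs are predicted and cases are few, a model that never predicts a case can win

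*Protocol article*

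**What the plan says.** Under *Primary outcome analysis: painCELL data* the protocol plans that "a randomised approach with at least a 20% holdout validation and test dataset will be employed". It continues: "For the categorical selection hypotheses, several classification techniques will be applied in parallel". The winner is then chosen: "The best-performing model will be identified based on the highest accuracy and lowest error rate". A confusion matrix follows, for the winner only. Sensitivity, specificity, AUC and balanced accuracy play no part in the choice; the ROC curves under *Secondary outcome analysis: painHS data* belong to the imaging analysis.

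The hypotheses to be classified are not listed. The one worked example is the knee contrast: "when testing the model for Healthy synovial sample Controls and the contralateral painful knee, Healthy blood sample Controls data will be excluded".

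Other places point to the psychological measures as further targets:
- *Abstract, Methods and analysis*: "Multivariable statistical and machine-learning approaches will relate biomarker profiles to pain and psychological PROMs".
- *Clinical assessment and questionnaires* turns the scores into classes: "an HADS-A or HADS-D score ≥8 will be categorised as the presence of anxiety or depression, respectively". For the PCS, "A score of 30 or higher is considered clinically relevant catastrophising", so that "patients will be considered pain catastrophizing (PC) or non-PC patients".
- The painCELL section puts pain scores and mental state into the same data file as the cytokine data.
- *Data analysis plan* counts machine learning among the secondary analyses, which cover anxiety, depression and catastrophising, and labels them all exploratory.

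No expected prevalence of these classes is given, and the text does not say whether the split is stratified.

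**The concern.** Accuracy weights each class by its share of the sample. When one class is small, a rule that assigns everybody to the larger class scores that class's share without using any biomarker. Ranking five or so classifiers on accuracy can therefore prefer one that has collapsed to this rule over one that does separate cases from non-cases.

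The hold-out is also very small: 20% of 20 patients is 4 people, and 20% of 40 participants is 8. Few or no cases may fall in it. With none, sensitivity cannot be estimated and the confusion matrix cannot show that the winner never finds a case. With some, the matrix would show it, but only after the choice has been made.

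At stake is how the second secondary aim (immune response and psychological factors) is read. A high accuracy that a constant guess would match could be taken as a biomarker signal and carried into the later work that this hypothesis-generating study is meant to inform.

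**Working it through.** The protocol gives no figure for classifier performance or class sizes. Its sample-size calculation concerns the EC50 comparison, so there is no plan figure to reproduce on this point.

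**Inputs from the protocol.** 20 patients and 20 healthy controls; hold-out of at least 20%; selection on accuracy.

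**Assumptions.** The number of cases k; a hold-out of exactly 20% drawn by simple random sampling; a comparator classifier with sensitivity = specificity = s whose errors are independent between people.

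**Step 1: accuracy of a rule that never predicts a case.** Expected accuracy = 1 − k/N.
- 10% prevalence: 0.90; 20%: 0.80; 30%: 0.70.
- The comparator's expected accuracy is s at any prevalence. The constant rule is ahead in expectation when 1 − k/N > s. With 4 of 20 positive that is 0.80 against 0.75; against s = 0.85 it is behind.
- Balanced accuracy of the constant rule = (0 + 1)/2 = 0.50 at any prevalence.

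**Step 2: chance that the hold-out has no case.** P = C(N − k, h)/C(N, h).

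| N | h | k | Calculation | P(no case) |
|---|---|---|---|---|
| 20 | 4 | 2 | 3060/4845 | 0.63 |
| 20 | 4 | 4 | 1820/4845 | 0.38 |
| 20 | 4 | 6 | 1001/4845 | 0.21 |
| 20 | 4 | 8 | 495/4845 | 0.10 |
| 40 | 8 | 4 | 30260340/76904685 | 0.39 |
| 40 | 8 | 8 | 10518300/76904685 | 0.14 |
| 40 | 8 | 12 | 3108105/76904685 | 0.04 |

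For a 20:20 contrast with h = 8, the chance that a given group is absent is C(20,8)/C(40,8) = 125970/76904685 = 0.0016.

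**Step 3: how often the constant rule wins on the hold-out (N = 20, k = 4, h = 4).** Let x be the number of cases in the hold-out. The constant rule gets 4 − x right. The comparator gets a + b right, with a ~ Bin(x, s) and b ~ Bin(4 − x, s). Weight P(a + b < 4 − x) by the hypergeometric probability of x:

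| x | P(x) | constant rule strictly better, s = 0.75 | s = 0.85 |
|---|---|---|---|
| 0 | 0.3756 | 0.6836 | 0.4780 |
| 1 | 0.4623 | 0.2617 | 0.1095 |
| 2 | 0.1486 | 0.0508 | 0.0120 |

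The terms x = 3 and x = 4 add less than 0.0001.
- s = 0.75: 0.2568 + 0.1210 + 0.0075 ≈ 0.385. Counting ties, 0.731.
- s = 0.85: 0.1796 + 0.0506 + 0.0018 = 0.232. Here the constant rule is strictly worse in 0.387 of splits.
- With 8 of 40 positive, h = 8 and s = 0.75: strictly better 0.468, at least tied 0.712.

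**The case against.** **The targets are inferred.** The classifier text names no PROM, it sits under the primary outcome, and its worked example is 20:20. *Sample size calculation* describes psychological modelling by limiting models to one psychological variable each, which reads as regression. This stands as a limit: the point is conditional. The abstract, the dichotomisation and the shared data file still make these classes plausible targets, and for them the selection rule is written down, not left open.

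**Stratification.** A reader might infer that the split is unstratified. The text says only that it is randomised; a random split can be stratified, and an article may leave that detail to a fuller plan. The no-case probabilities therefore describe a simple random split, not a stated defect.

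**Prevalence and comparator.** A reader might also infer that the hold-out will usually lack cases, or that accuracy always picks the wrong model when classes are unequal. Neither follows. The no-case risk is 14% with 8 cases among 40 and 4% with 12, and against a comparator at 0.85 the constant rule loses more often than it wins.

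**The balanced contrasts.** An uneven hold-out from a 20:20 contrast does not show a majority rule winning: the training set then leans the other way, and a majority rule learned there is penalised on the hold-out.

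**Limited consequence.** The analyses are labelled exploratory, and the confusion matrix would expose a winner that predicts no cases if the hold-out contains some. Both are true and lower the weight of the point. The matrix nevertheless comes after selection and covers only the winner, so it cannot correct the choice.

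**Conclusion.** The point holds in conditional form. Accuracy is the sole stated selection rule. It does little harm for the 20:20 contrasts, but it is a poor rule if the HADS and PCS classes are predicted and turn out unequal. The harm arises when the majority share is near or above the accuracy of the informative model. At an assumed 4 cases in 20 patients, a model that never predicts a case strictly beats one with sensitivity and specificity 0.75 in 39% of splits, and one with 0.85 in 23%.

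These sizes rest on an assumed prevalence, an illustrative comparator and a simple random 20% hold-out. The documents do not support saying that the published answer on psychological factors will mislead, only that the stated rule allows it. It should be changed because the change is nearly free and recruitment had not started when the protocol was written.

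**What to change.** In the classifier paragraph of *Primary outcome analysis: painCELL data*:
- Replace accuracy and error rate as the selection criterion by balanced accuracy (the mean of sensitivity and specificity) or AUC, estimated by repeated cross-validation stratified on the class being predicted, and report the same measure.
- Print the majority-class accuracy, 1 − k/N, beside each confusion matrix.
- Where a class has only about two members, report that it is too rare to classify. Stratification does not rescue this case: 2 of 20 gives 4 × 2/20 = 0.4 expected cases in a hold-out of 4.

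The cost is a few sentences and a few lines of code, with no new data. The downside is that the headline figures may look less favourable: the constant rule falls from 0.80 to 0.50 at 20% prevalence.

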#### Secondary outcome analysis: painHS data

HS images are pre-processed as previously described.^41^ This will be followed by cell segmentation, carried out in an automatic approach using a parametric watershed algorithm with a partial set principal components (PCA) image. The channels employed in the PCA segmentation image are found through trial and test. This segmentation protocol will be augmented with additional manual segmentation using the phase contrast image and selecting cells at random. By estimation, this will yield 70–90 cells from each image, belonging to one of the following four sample groups: (1) blood samples from painful symptomatic osteoarthritis patients (participant group 1), (2) synovial fluid samples from painful symptomatic osteoarthritis patients (participant group 1), (3) synovial fluid samples from contralateral pain-free control knee (participant group 1) and (4) blood samples from pain-free controls (participant group 2).

After each cell is segmented from the background, a number of quantitative features are calculated using the segmented cells to parameterise the cell data, with the primary goal of delineating participant population membership. In particular, for each cell we will calculate ratios of mean channel intensities of pairs, correlation of channel pixel intensities and coherence of the statistics of the channel pairs. The feature data for all cells will then undergo a singular value decomposition as described previously.^40^ These uncorrelated variables are then further used for supervised discriminatory analysis.^40 41^ The LDA will provide another set of seven feature variables maximising the separation between the sample populations.^40^ These are then optimally projected by using the second linear discriminant analysis onto two dimensions to obtain a graphical representation, showing the optimal participant group separation. Subsequently, they are projected again using LDA on a single optimised dimension. Receiver operator curves will be plotted to assess the sensitivity and specificity of the approach.

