### Participants and eligibility criteria

Participants will be consecutively included after screening for eligibility and provided informed consent at the orthopaedic clinic of Noarlunga Hospital, Flinders Medical Centre, SALHN. The study planned to enrol 3 groups of participants: (1) 20 patients awaiting TKA including 20 *painful* knees with moderate to severe osteoarthritis, (2) 20 controls, the healthy contralateral *pain-free* knee of these 20 patients awaiting TKA and (3) 20 different healthy controls for venous blood measurements, age and sex matched healthy individuals with no pain complaints in general at that moment, and no function limitation or pain in any joint (no diagnosed osteoarthritis in both knees). This will result in 40 participants in total: Group 1: 20 patients with 20 *painful* knees with osteoarthritis that are awaiting TKA and 20 *pain-free* contralateral control knees of the same patients; Group 2: 20 *pain-free* control patients without any knee complaints.

Healthy controls are defined as individuals without knee pain or functional limitations in either knee. Radiographic imaging will not be performed in this group, as the primary focus of the study is the biological correlates of pain rather than structural osteoarthritis, and obtaining radiographs in asymptomatic individuals solely for research purposes would expose participants to unnecessary radiation. It is acknowledged that some asymptomatic individuals may have radiographic osteoarthritis; however, structural changes and pain symptoms are known to correlate only moderately.^13^,^17^

Inclusion criteria for eligibility for this study are (1) awaiting a unilateral primary TKA for symptomatic (painful) advanced osteoarthritis,^33^ (2) asymptomatic (pain-free) contralateral knee without functional limitation or pain (no or mild osteoarthritis), (3) otherwise good general health, (4) aged 18 years or over, (5) completion of all preoperative questionnaires and (6) providing informed consent.

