#### PainHS sample analysis

Venous blood samples collected in EDTA-coated vacutainer tubes and the synovial fluid collected in sodium citrate-coated tubes/sterile containers for the painHS test were frozen and stored at −80°C for later analysis. On the day of analysis, samples will be thawed in a 37°C water bath for 45 mins. The blood and synovial fluid will be washed with equal volumes of RPMI1640, centrifuged (240×g for 5 min) with supernatant removed and resuspended in 3–5 mL of RPMI. Cells of the blood and synovial fluid samples are counted and then placed on the imaging slides for HS imaging. An adapted fluorescence microscope (Olympus iX71) will be used with a 40×water U12 series objective (with wide transmission in UV range). LEDs with excitation wavelength bands centred at 334, 365, 385, 395, 405, 415, 425, 435, 455, 475, 495 nm, each about 10 nm wide produce close to monochromatic light to excite the sample’s auto-fluorescence. The corresponding sample emission will be measured with three epifluorescence filter cubes with the emission bands centred at 447 nm (60 nm wide), 587 nm (35 nm wide) and 700 nm long pass. Overall, in this work we use 18 spectral channels (ref) with the same channel numbering as used here,^40^ and each field of view will be imaged in all these 18 channels forming a HS image. Images are captured by a digital camera C1140, OCRA Flash 4.0 (Hamamatsu). Images will then be saved and digitally transferred for digital analysis by the Neuroimmunopharmacology laboratory.

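### Hyperspectral analysis: seven discriminant variables cannot come from four sample groups, and the cell-level SVD, LDA and ROC chain states no participant-level validation

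*Protocol article*

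**What the plan says.** The section on the secondary outcome analysis of painHS data in the Protocol article expects a yield per image ("By estimation, this will yield 70–90 cells from each image"), each cell "belonging to one of the following four sample groups": patient blood, painful-knee synovial fluid, contralateral-knee synovial fluid and control blood.

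The steps then run as follows:

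- Features are built from pairs of spectral channels.
- "The feature data for all cells will then undergo a singular value decomposition".
- A first LDA follows: "The LDA will provide another set of seven feature variables maximising the separation between the sample populations".
- A second LDA reduces these variables to two dimensions, for plotting the groups.
- A third LDA reduces them to one dimension.
- The last step is the assessment of performance: "Receiver operator curves will be plotted to assess the sensitivity and specificity of the approach".

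The section mentions no training and test split, no cross-validation and no grouping of cells by participant. It refers to earlier work for the SVD and LDA steps. A hold-out of at least 20% is described in the preceding section, on painCELL data, without saying whether cells, samples or participants are split. The data analysis plan calls all secondary analyses exploratory.

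**The concern.** There are two separate points.

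**The number seven.** LDA finds directions that separate class means, and the number of classes limits how many such directions exist. Seven does not fit the four groups named in the same section.

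**The unit of validation.** The chain uses the group labels in up to three successive fits, on many cells per sample from few people. Cells from one sample share that person's biology, collection, freezing and thawing. A classifier can therefore learn to recognise samples instead of pain status. If the ROC is not drawn on people the fit has never seen, sensitivity and specificity can look better than they are. The ROC is the only performance measure given for painHS, and the study is meant to inform later biomarker work, so an optimistic curve would carry forward.

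**Working it through.** **1. The stated figure**

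Inputs: K = 4 groups and seven variables, both from the painHS analysis section.

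Number of discriminants ≤ min(p, K − 1), because the between-group scatter matrix is built from K group means around their overall mean and so has rank at most K − 1.

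- K = 4: at most 3.
- K = 2: at most 1.
- Seven requires K − 1 ≥ 7, so K ≥ 8.

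Numerical check with 30 features: four classes gave eigenvalues 7.38, 6.23, 3.44 and then zero. Two, three and eight classes gave 1, 2 and 7 non-zero eigenvalues. The plan's seven is not reproduced from four groups. The later reductions to two dimensions and to one are possible from three axes.

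**2. Optimism when there is no group difference**

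Inputs from the Protocol article: 20 patients and 20 controls ("This will result in 40 participants in total"), hence 20 samples in each of the four groups, and 70–90 cells per image. For the feature space, "in this work we use 18 spectral channels", so there are 18 × 17 / 2 = 153 channel pairs. If each of the three feature types is computed for every pair, that is 3 × 153 = 459 features before the SVD. This count is derived, not stated.

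Assumptions, because the article does not give them: one image of 80 cells per sample; p retained SVD components, from 7 to 100; within-sample correlation (ICC) from 0 to 0.5. Samples were simulated as independent, ignoring that three of the groups come from the same patients.

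Method: 4 × 20 × 80 = 6,400 cells with no group difference; LDA to three axes, then two, then one; ROC for patient blood against control blood; 30 runs per setting. Mean AUC:

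| p | ICC | Training cells | 20% of cells held out | 20% of participants held out |
|---|---|---|---|---|
| 7 | 0 | 0.52 | 0.50 | 0.50 |
| 20 | 0.05 | 0.58 | 0.56 | 0.49 |
| 20 | 0.2 | 0.66 | 0.65 | 0.48 |
| 50 | 0 | 0.55 | 0.50 | 0.49 |
| 50 | 0.2 | 0.73 | 0.72 | 0.50 |
| 100 | 0.2 | 0.81 | 0.79 | 0.50 |
| 100 | 0.5 | 0.92 | 0.91 | 0.53 |

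The true value is 0.5 throughout. With uncorrelated cells, a cell-level hold-out is enough. Once cells in a sample are correlated, it removes almost none of the optimism. Holding out participants gave 0.48 to 0.53 over all settings.

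**3. Fluid and pain**

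The four groups are two fluids, each with a painful and a pain-free class. A two-dimensional LDA display needs at least three classes (K − 1 ≥ 2). Any three of the four groups include both fluids, since each fluid supplies only two. With classes formed from the listed groups, the display therefore mixes fluids. Its axes follow the largest differences between class means. Blood and synovial fluid differ as materials and, according to the PainHS sample analysis section, are collected in different tubes (EDTA against citrate). Clear separation on such a plot need not reflect pain.

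**The case against.** - **The ROC data are not stated.** A reader might infer that the curves are drawn on the training cells. The article does not say so: its mention of all cells concerns only the input to the SVD. The painCELL section does keep test data out of training and names LDA among its methods; whether that reaches painHS is unclear, not excluded. An article may also leave validation detail to the full protocol. This stands, and resubstitution cannot be asserted. What remains is that the described hold-out names no split unit, and a random split of cells would not be adequate.
- **The size is uncertain.** A reader might conclude that the analysis will show separation when there is none. The training-cell AUC under the null runs from trivial (0.52) to severe (0.92), depending on quantities the article does not give. It can mislead; that it will is not shown.
- **Seven may have a source.** It may come from a design with eight or more classes or from another procedure in the cited work. The documents cannot settle this. As written for these groups, it still needs correction or explanation.
- **The ROC may be within fluid.** A single dimension with an ROC suggests a two-group contrast. The primary comparisons are within fluid, and the painCELL section excludes irrelevant groups for each test. The mixing of fluids therefore applies to the joint projection; it is not established for the ROC.
- **The analysis is exploratory.** This limits the consequences, but the label does not correct a biased sensitivity or specificity.

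**Conclusion.** The concern holds as two separate points, both of which should be fixed in a secondary, exploratory analysis.

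The first is certain: ordinary LDA on the four named groups yields at most three axes, so seven cannot be obtained.

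The second is a cheap improvement. The chain is described for cells, without participant-level validation. Under the null, the AUC can reach 0.92 on training cells and 0.91 on held-out cells, against about 0.5 on held-out participants. These sizes rest on the assumed ICC, number of components and one image of 80 cells per sample.

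Two further inferences are not supported. The figure seven does not cause the optimism, since the simulation used three axes and still showed it. Nor would an optimistic ROC make the third secondary aim look successful: that aim relates imaging hues to IL-1β expression, and an ROC for group membership does not test it. The primary painCELL analysis is not affected by this point.

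**What to change.** 1. Correct the number seven, or state the class structure or other procedure that produces it.
2. Run two separate two-class analyses, with one discriminant axis each: blood (patients against controls) and synovial fluid (painful against contralateral knee).
3. Validate by holding out whole participants or matched pairs. Keep both knees of a patient in the same fold, and refit the SVD and LDA within each fold.
4. Draw the ROC on out-of-fold scores, summarised to one value per participant sample, with a bootstrap confidence interval that resamples participants.
5. If a joint four-group plot is kept, label it as descriptive and say that it includes differences between fluids.

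The cost is wording and a little more code; the article says recruitment has not begun, and no extra samples are needed. The downside is that the ROC curves will be less flattering and less precise, because they rest on about 20 samples per group instead of many cells.

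### The painHS plan promises seven LDA variables, but its four sample groups allow at most three and a two-group pain contrast only one

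*Protocol article*

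**What the plan says.** The chain is described in the Protocol article under *Secondary outcome analysis: painHS data*. Segmented cells are described as "belonging to one of the following four sample groups": patients' blood, synovial fluid from the painful knee, synovial fluid from the contralateral pain-free knee, and controls' blood. Features are computed for each cell "with the primary goal of delineating participant population membership". They are built from pairs of imaging channels, and *PainHS sample analysis* says that "each field of view will be imaged in all these 18 channels forming a HS image".

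After a singular value decomposition (SVD) of the features, the plan states: "The LDA will provide another set of seven feature variables maximising the separation between the sample populations". Two more projections follow: "These are then optimally projected by using the second linear discriminant analysis onto two dimensions", and then "Subsequently, they are projected again using LDA on a single optimised dimension". The chain ends with: "Receiver operator curves will be plotted to assess the sensitivity and specificity of the approach".

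The section does not name the class labels used at any of the three LDA steps, nor the binary contrast behind the ROC. The two pain contrasts in the article (painful against contralateral knee in synovial fluid, patients against controls in blood) stand in the introduction to the *Data analysis plan*, where they describe the primary analyses.

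**The concern.** The number of discriminants in an LDA is limited by the number of classes. A plan that lists four classes and promises seven discriminants contradicts itself within one section, and the step that feeds all later ones cannot be carried out on the stated groups.

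What is at stake is what the reported sensitivity and specificity mean. The four groups differ in two ways at once: fluid (blood or synovial fluid) and pain status. An LDA fitted to all four maximises overall separation, and its leading axis need not separate painful from pain-free samples. If the labels at the last step stay open, a ROC could partly describe how well blood cells are told apart from synovial cells. Under *Sample collection*, the painHS test is meant to look for phenotypic differences between participant groups, so the labels are central to this analysis.

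**Working it through.** **Inputs.** Discriminants stated: 7. Sample groups stated: K = 4. Pain contrasts in the article: K = 2 each. Imaging channels: 18. The number of input features p is not fixed in the article.

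**Formula.** The between-class scatter matrix is S_B = Σ n_k (m_k − m)(m_k − m)ᵀ, where m_k are the class means and m is the overall mean. Because Σ n_k (m_k − m) = 0, the K deviations span at most K − 1 dimensions. The number of discriminants is therefore min(p, K − 1).

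**Numbers put in.**
- Four groups: min(p, 3), so at most 3. Shortfall against the plan: 7 − 3 = 4.
- Two groups: min(p, 1) = 1. Shortfall: 7 − 1 = 6.
- Seven discriminants need K − 1 ≥ 7, so K ≥ 8.
- Feature supply does not explain the seven: 18 × 17 / 2 = 153 channel pairs are available per feature type.

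The plan's figure of seven could not be reproduced from its own groups.

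**Numerical check** (simulated data, p = 30 assumed; eigenvalues of S_B against the within-class scatter):

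| K | Non-zero discriminants |
|---|---|
| 2 | 1 |
| 3 | 2 |
| 4 | 3 |
| 7 | 6 |
| 8 | 7 |

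For K = 4 the eigenvalues were 41.73, 7.66 and 1.63, then zero.

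**Other routes to seven from four groups.**
- One LDA per pair of groups: 4 × 3 / 2 = 6.
- One group against the rest: 4.
- One LDA per two-way split of the groups: 2³ − 1 = 7. These seven directions had singular values 2.11, 1.25 and 0.99, then about 10⁻¹⁴. They carry only three independent variables, and a second LDA on all seven would meet a singular within-class matrix.
- Every sample as its own class (20 + 20 + 20 + 20 = 80): 30 discriminants in the simulation, limited by p = 30. This is not seven, and the article does not describe it.

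**Later steps.** Three discriminants are enough for a projection onto two dimensions and then onto one. With K = 2 there is only one axis, so LDA could not supply a two-dimensional plot for a single pain contrast.

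**Do the labels of the later LDAs matter?** Two simulated illustrations used four groups, 20 features and 400 cases per group, with assumed group means.
- Same four labels again: the second LDA returned the same eigenvalues (2.412, 1.324, 0.609), and its first axis correlated 1.000 with that of the first LDA.
- Two-group labels on the three first-stage scores (one draw, in-sample AUC):

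| Contrast | Correlation with first four-group axis | AUC on four-group axis | AUC on two-group axis |
|---|---|---|---|
| Blood: patients vs controls | 0.73 | 0.80 | 0.91 |
| Synovial fluid: painful vs pain-free knee | 0.95 | 0.97 | 0.99 |
| Pooled: both patient pain groups vs both pain-free groups | 0.46 | 0.60 | 0.81 |

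These values depend on the assumed means and predict nothing for this study. They show only that the choice of labels changes the final axis and the ROC.

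**The case against.** The strongest defence is that the section leans on a cited method source. Seven might mean retained SVD components, a different class structure or a variant that is not Fisher's LDA, and a condensed article may leave detail to its references. This stands as a possible explanation of where the number came from. It does not make seven correct for the four groups listed here, and the sentence presents the seven as output of the LDA.

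The work is also secondary, and the article says plainly that such analyses are exploratory. That stands and limits the weight of the point.

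A reader might infer more than the document supports:
- *That no ROC can be produced.* Only the seven-variable step fails. An analyst using the four stated groups gets three axes and can go on to two dimensions, one dimension and a ROC.
- *That the second and third LDAs are redundant.* This holds only if the labels stay the same. The article does not say that they do, and a later step with two-group labels is not redundant.
- *That a two-dimensional plot is impossible.* It would be for a two-group contrast, but the section lists four groups and does not tie the plot to two of them.
- *That the analyst would have to turn participants or subsets into classes.* Nothing in the text suggests this.
- *That secondary aim 3 would go unanswered.* The article frames that aim as the relation between imaging hues and IL-1β, not as discrimination by pain group.

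**Conclusion.** The point holds for the count. On the four stated sample groups, LDA gives at most three discriminant variables, so at least four of the seven cannot exist. For either two-group pain contrast, six of the seven cannot. This is a rank result and does not depend on the simulated data. It assumes standard LDA with the groups that the section lists.

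The need to state the labels follows from the same section. A ROC requires a binary contrast, and the four groups mix fluid with pain status. How far fluid type would shape the result cannot be judged from the article.

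The consequence is limited to one secondary, exploratory analysis. The primary EC50 comparison and the sample size do not depend on it.

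**What to change.** In *Secondary outcome analysis: painHS data*:

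1. Replace seven with at most three for the four-group LDA. If seven is the number of SVD input features kept, say so and separate it from the number of discriminants.
2. Describe the two-dimensional four-group plot as descriptive.
3. State that the final one-dimensional LDA and the ROC use two-group labels within one fluid: patients against controls for blood, and painful against contralateral pain-free knee for synovial fluid.
4. Name the labels of each LDA step. With labels stated, the later steps can stay.

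The cost is a few sentences. No new samples or measurements are needed, and the article reports that no participant data have been generated yet, so the change can be made before any analysis.
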